#### Sample size

Power calculations are based on expected progress in use of communication strategies (the Communication Strategies Scale of the Hearing Handicap and Disability Inventory), which has been the primary outcome of previous studies in persons with hearing loss [41]. In a previous RCT by Kramer et al. (2005) on the effectiveness of a home education program for older adults with hearing impairment only, the mean difference in communication skills between the intervention and control group was about 0.5 (SD = 0.8) [41]. Sample size calculations of this RCT are based on a linear mixed models and confirmed by some simulations (data not shown). Sixty-two participants per arm, with adjustment for clustering by 8 therapists in the intervention condition, provide a power of 0.80 (1-β) with alpha 0.05 (two-sided significance level), to detect a 0.5 difference between trial arms after 3 months (corrected for the differences at baseline), after taking into account a 20% dropout rate.

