**DSL patients**		
*Primary outcome measures*		
Hearing aid fitting, hearing aid use and satisfaction	X	X
Difficulties with hearing aid use and maintenance	X	X
Change in hearing aid use (IOI-HA) [65,66]		X
Change from communication strategies (IOI-AI) [67]		X_i_
Communication (CPHI-communication strategies) [68]	X	X
*Secondary outcomes*		
Health (subjective health)	X	X
Health related quality of life (EuroQol-5 Dimensions (EQ-5D)) [69]	X	X
Coping with hearing impairment (CPHI-personal adjustment) [68]	X	X
Vision-related quality of life (LVQOL) [70,71]	X	X
Loneliness (Loneliness scale) [72,73]	X	X
Fatigue (FAS) [74]	X	X
Participation (parts of D-AI-interpersonal interactions and relationships) [75]	X	X
Autonomy (PAQ) [76]	X	X
Evaluation of intervention		X_i_
*Covariates*		
Patient characteristics (e.g. age, gender, education, living arrangement)	X	
Disability characteristics (eye condition, VA, self-perceived vision (VFQ25-general vision subscale [77]), hearing condition, hearing loss (speech-reception-threshold in noise))	X	
Cognition (6-item screener MMSE) [78]	X	
Depressive symptoms (CES-D) [79]	X	X
Major life events between baseline and follow-up		X

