**Communication partners**		
*Primary outcomes*		
Coping with hearing loss (HHDI ‘reactions of others’ scale) [80]	X	X
Change from hearing aid use (IOI-HA-SO) [67]		X
Change from communication strategies (IOI-AI-SO) [67]		X_i_
Quality of life (CarerQoL) [81]	X	X
Evaluation of intervention		X_i_
*Secondary outcomes*		
Chronic fatigue (FAS) [74]	X	X
Depression (CES-D) [79]	X	X
Health (subjective health, EQ-5D) [69]	X	X
*Covariates*		
Demographic characteristics (e.g. age, gender)	X	
Relationship with patient (sort and quality of relation)	X	X
Self-efficacy (G-SES) [82]	X	X

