#### Primary outcome measures

*Difficulties with hearing aid use and maintenance* will be measured with questions on problems with hearing aid use and maintenance, e.g. “How difficult is it for you to insert your hearing aid?” or “How difficult is it for you to change your hearing aid batteries?”. Questions on *hearing aid fitting, hearing aid use and satisfaction* will be based on the Questionnaire for evaluation of hearing aid fitting, e.g. hours of hearing aid use, use of hearing aids in different situations, and appreciation of hearing aids [84]. *Self-reported change from hearing aids* is measured with the Dutch version of the widely used International Outcome Inventory for hearing aids (IOI-HA) [65,66,85]. The Communication Profile for the Hearing Impaired (CPHI) is an instrument to measure coping behavior related to hearing impairment and is divided into two domains: ‘Communication Strategies’ and ‘Personal Adjustment’ [68]. The ‘Communication Strategies’ domain of the Dutch 35-item version of CPHI will be used to measure *Communication* (coping behavior in communicative situations) and consists of three subscales: ‘Maladaptive Behavior’; ‘Verbal Strategies’ and ‘Non-verbal Strategies’ [68]. *Self-reported change from communication strategies* reported by the participant is measured with the Dutch version of the International Outcome Inventory for alternative strategies (IOI-AI) [67]. Both measures have been used for evaluation of communication programs by, e.g. Kramer et al. (2005) and Hickson et al. (2005) [41,48]).

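### The 80% power is tied to an HHDI scale that patients are not given, so it is not shown to apply to the CPHI communication outcome

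*Protocol article*

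**What the plan says.** The Sample size section takes as its outcome "the Communication Strategies Scale of the Hearing Handicap and Disability Inventory". From an earlier randomised trial of home education, whose participants had hearing loss alone, it takes this result: "the mean difference in communication skills between the intervention and control group was about 0.5 (SD = 0.8". The planned size is given as "Sixty-two participants per arm, with adjustment for clustering by 8 therapists in the intervention condition". These numbers are said to "provide a power of 0.80 (1-β) with alpha 0.05 (two-sided significance level". The stated target is "to detect a 0.5 difference between trial arms after 3 months (corrected for the differences at baseline". The figure allows for 20% dropout.

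The outcome sections name a different instrument. Table 2 lists, among the patients' primary outcomes at baseline and 3 months, "Communication (CPHI-communication strategies) [68". The Primary outcome measures section confirms the choice, saying of Communication Strategies that this "domain of the Dutch 35-item version of CPHI will be used to measure" how patients communicate. It describes that domain as three subscales (maladaptive behaviour, verbal strategies and non-verbal strategies).

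The HHDI appears in Table 2 only for communication partners: "Coping with hearing loss (HHDI", followed by the name of its reactions-of-others scale. The Communication partner section describes the same use.

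**The concern.** This is the article's only sizing claim, and it is fixed in raw points on a named scale. A raw difference of 0.5 has a given power only in relation to the SD of the score being analysed. If the scale used for sizing is not the one patients complete, neither the 0.5 nor the 0.8 is known to describe the outcome that will be tested.

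No other patient measure fills the gap. The IOI-AI also concerns communication strategies, but Table 2 marks it as assessed in the intervention group only, so it gives no contrast between arms. That leaves the CPHI domain.

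At stake is how a CPHI result will be described. A reader would take it as coming from a test with 80% power for a 0.5-point effect, and the article does not establish that.

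**Working it through.** **1. The instruments side by side**

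- Sample size: Communication Strategies Scale, attributed to the HHDI.
- Table 2, patients: CPHI communication strategies (both arms, both visits); IOI-AI (intervention arm only, follow-up only). No HHDI scale.
- Table 2, communication partners: HHDI reactions-of-others scale, used for coping.

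The scale named for power is therefore not a listed patient outcome. No difference or SD in the article is labelled as CPHI.

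**2. Can 62 per arm be reproduced from the stated inputs?**

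Inputs from Sample size: difference 0.5, SD 0.8, two-sided alpha 0.05, power 0.80, 8 therapists in the intervention arm, 20% dropout. No intraclass correlation (ICC) or baseline correlation is given.

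- Standardised difference: 0.5/0.8 = 0.625.
- Without clustering: n = 2(1.96 + 0.8416)²/0.625² = 40.2, so 41 per arm; 41/0.8 gives 52 after dropout.
- Completers planned: 62 × 0.8 = 49.6 per arm, or 49.6/8 = 6.2 per therapist.
- Power with 49.6 per arm and no clustering: 87.5%.
- Inflation available for clustering: 49.6/40.19 = 1.234. If only the intervention arm is clustered, its design effect is 2 × 1.234 − 1 = 1.468, which implies an ICC of 0.468/(6.2 − 1) = 0.09.
- Check, same formula: power is 83% at ICC 0.05 and 79% at ICC 0.10.

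The stated correction for baseline differences would change the back-solved ICC. With an assumed baseline correlation of 0.5, the variance factor is 1 − 0.5² = 0.75 and the unclustered need is 40.19 × 0.75 = 30.1. Then 49.6/30.14 = 1.646, the design effect is 2 × 1.646 − 1 = 2.29, and the ICC is 1.29/5.2 = 0.25.

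So 62 per arm is compatible with the stated inputs over a range of assumptions. It cannot be confirmed without the sponsor's own, and nothing here shows a calculation error.

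**3. What depends on the instrument (illustration only)**

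Keep the clustering implied by the stated 80% without baseline credit. The standard error in SD units is √((1.468 + 1)/49.6) = 0.223, and power = Φ((0.5/SD)/0.2231 − 1.96):

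| Assumed SD | Power for a 0.5-point difference |
|---|---|
| 0.6 | 96% |
| 0.7 | 89% |
| 0.8 | 80% |
| 0.9 | 70% |
| 1.0 | 61% |
| 1.2 | 46% |

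The SDs are assumptions. A different instrument would also change the expected difference, which is held at 0.5 here. The table shows only that the 80% carries over if the CPHI ratio of difference to SD is about 0.625, and that it can move in either direction otherwise.

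**The case against.** The strongest reply is that HHDI is a slip of the pen for CPHI. The CPHI domain also carries the name Communication Strategies. The Primary outcome measures section, after describing the CPHI and the IOI-AI, says that both measures were used to evaluate earlier communication programmes. It cites as an example the same trial that supplies the 0.5 and 0.8. If so, the figures may come from the very domain that patients complete, and the power claim may be sound. This reading is plausible, and the article alone cannot settle it.

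A reader might infer from the mismatch that the 80% does not apply, or that the trial is underpowered. The document does not support that. It gives no CPHI values against which to judge, and the sample size fits its stated inputs. A reader might also take the ICC of 0.09 as the sponsor's value. It is only back-solved, and it rises to about 0.25 once an assumed baseline correlation of 0.5 is credited.

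It can also be said that the choice between a domain score and subscale scores is commonly left to an analysis plan. That is fair as far as scoring rules go, and the absence of those rules is not the point here. What stands is that the article states an instrument in its power claim that conflicts with its own outcome list, and the slip reading does not remove that. Even then the text names the wrong instrument and leaves open whether 0.5 (SD 0.8) belongs to one subscale or to the whole domain.

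**Conclusion.** The point holds as an inconsistency between the sizing claim and the outcome list. Either the instrument in Sample size is misnamed, or the trial is sized on an outcome it does not measure in patients. In both cases the paragraph is wrong as written, and the 80% is not shown to apply to the CPHI communication outcome. It is not shown to fail either, and 62 per arm is not shown to be miscalculated.

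The effect on power cannot be sized from the document. It is nil if 0.5 (SD 0.8) was observed on the CPHI score to be analysed. Otherwise it depends on a CPHI difference and SD that are not given. The conclusion that the instruments conflict rests on the text alone and needs no numerical assumption.

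**What to change.** - Reconcile the Sample size section with Table 2 and correct the instrument name if it is a slip.
- Name the CPHI score that carries the power: one predefined Communication Strategies score or one subscale.
- Say whether the difference of 0.5 (SD 0.8) was observed on that score.
- If it was not, restate the claim as the standardised difference that 62 per arm can detect: 0.625 SD at 80% power, under the sponsor's own ICC and baseline-correlation assumptions, which should be stated alongside it. Convert this to CPHI points with the baseline SD pooled over both arms without reference to allocation. For example, a baseline SD of 1.0 would give 0.625 × 1.0 = 0.625 points. The conversion treats the 0.8 as an SD of scores rather than of changes, and the sponsor should confirm this.

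The cost is a rewording of one paragraph and, if needed, one arm-blind SD calculation. The restated power for 0.5 points may turn out less favourable than 80%. No extra patients and no change of design are needed.

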#### Economic evaluation

In addition to the RCT, an economic evaluation will compare costs and consequences from a societal perspective of an intervention group receiving the DSL protocol compared with a waiting list control group. Therefore, all costs and consequences of the DSL protocol will be taken into account for patient, communication partner and society. The incremental cost-effectiveness ratios (ICER) will be calculated; the difference in mean costs between intervention and control group will be divided by the difference in outcome measures between the two groups. Because costs data are generally skewed, non-parametric bootstrapping with 5000 replications of both intervention and control group will be used to derive 95% confidence intervals for the ICER. Bootstrapped cost-effectiveness pairs will be plotted in a cost-effectiveness plane and cost-effectiveness acceptability curves will be estimated [90].

## Discussion

Especially among visually impaired elderly, dual sensory loss (DSL) is highly common. Of all the related difficulties, communication is perhaps the most challenging and it may negatively affect a patient’s health and wellbeing. We expect the newly developed DSL protocol to reduce these difficulties. This may lead to better hearing aid use, improved use of effective communication strategies and hence, better quality of life, health and wellbeing. This paper describes the ‘Dual Sensory Loss-protocol’ and the design of a multicenter international RCT to determine the effectiveness and cost-effectiveness of the DSL protocol.

In the development of the DSL protocol, designed for OTs working in low vision rehabilitation, we obtained information from the literature, which we complemented with interviews and discussions with patients and professionals (working in ear and eye care). The trial will test the effectiveness of the additional DSL protocol compared to a waiting list control group on use and maintenance of hearing aids; communication; coping with a dual sensory impairment; social participation and quality of life of the patient and communication partner; and cost-effectiveness from a societal perspective.

The development of the protocol and design of the RCT required decisions as to which professionals would be most suitable to perform the protocol, and which DSL patients should be included in the trial.

Firstly, the DSL protocol consists of three chapters suitable for different rehabilitation professionals. On the one hand, the first two chapters of the DSL protocol focus on maximizing use of the senses with the use of hearing aids; other assistive devices; and minor adaptations to the living environment; these are considered highly suitable topics to be handled by OTs. On the other hand, the last chapter focuses on psychosocial issues: it discusses communication difficulties, psychosocial problems, coping with dual sensory impairment, and also teaches communication strategies; some consider that these topics are more suitable for social workers. To be able to build a relationship of trust, the patient can best be handled by one professional, and we decided OTs are the most competent. Secondly, we decided to recruit DSL patients who already received usual low vision and audiology care, i.e. patients who possess hearing aids and who have received low vision rehabilitation. This allows us to investigate the added value of the DSL protocol compared to a waiting list control group (which was allowed to receive other interventions if needed).

Several studies have aimed to meet the urgent need for evidence-based protocols and interventions in rehabilitation [91-94]. However, until now, little attention has been paid to the development and evaluation of interventions for the vulnerable group of DSL patients, who represent an urgent research need [47]. Our innovative study on rehabilitation of DSL for use in low vision rehabilitation is one of the few addressing these needs in older patients with age-related DSL. Additionally, low vision patients who seek help for their impairment at multidisciplinary low vision rehabilitation centers will likely be open to rehabilitation in general. We believe our DSL protocol will assist frail elderly with DSL in low vision rehabilitation; it addresses urgent needs not yet addressed by other interventions.

However, there are limitations to the study concerning both the protocol and the RCT. First, the DSL protocol was developed for patients with some residual vision and hearing, which concerns the vast majority of DSL patients [95], and focuses on maximum use of both senses. Therefore, the protocol is less suitable for totally blind and/or deaf patients; information on teaching tactile sign language is not incorporated. Also, although we believe that the DSL protocol is comprehensive and includes various forms of rehabilitation, eccentric viewing is not included. It maybe worthwhile for future implementation of the protocol to include eccentric viewing strategies to improve speech reading in patients with central scotoma [38]. Other limitations are related to the choice of a pragmatic instead of an explanatory trial. Further standardization of the DSL protocol would increase the ability to adequately evaluate the effectiveness. Standardization of the protocol could be improved by, e.g. standardizing the exact amount of time per exercise and chapter, and the number of sessions per patient. However, in daily practice it is very important to adapt to the needs of the individual patient, e.g. severity of vision and hearing impairment; or other impairments/limitations due to comorbidity, learning abilities, fatigue or concentration. For this reason, the current DSL protocol is adaptive to suit the needs of the individual patient. In line with the suboptimal standardization, the rather heterogeneous study population could be another limitation. However, to ensure generalizability, the study population had to reflect the variations among patients which occur in actual rehabilitation practice and to best represent patients in whom the treatment would be applicable.

Second, due to budgetary restrictions it was not possible to provide information on the long-term effects. Third, blinding of participants and OTs is not possible since no placebo treatment is included in the study to account for the placebo effect. Participants may report change as a result of simply meeting with an empathetic professional each week to discuss problems. Therefore, the effect of the DSL protocol is the total difference between groups, including both treatment and associated placebo effects. This has both advantages and disadvantages: a disadvantage is that the pure effect of the DSL protocol’s content remains unclear whereas, on the other hand, reality is best reflected. This pragmatic trial provides the best reflection of the likely rehabilitation outcome in actual practice.

This study provides useful information on DSL. Also, if the trial shows the DSL protocol to be effective, this will allow multidisciplinary low vision rehabilitation centers to provide an evidence-based treatment protocol for DSL patients. The DSL protocol will be an important tool for OTs to assist their older patients with DSL in the use of hearing aids, to maximize use of the senses, and to teach patients and/or communication partners specific skills to improve communication.

However, DSL needs more attention in other care settings (besides low vision rehabilitation), such as nursing homes and audiology rehabilitation. It is estimated that about 2% of the elderly who consult a hearing healthcare professional experience such visual impairment to such extent, that it limits the perception of facial cues for communication [54]. Although future research on DSL in audiology care is recommended, rehabilitation of DSL in the setting of audiology care requires even more effort. Hearing impairment in the elderly occurs much more frequently than visual impairment. Therefore, DSL in audiology rehabilitation is less common, so that more patients need to be screened to detect patients with DSL. In addition, low vision and hearing rehabilitation is organized in different ways. For example, in the Netherlands, many older adults with hearing loss in the Netherlands do not consult a multidisciplinary audiology rehabilitation center but go directly to a hearing aid dispenser; this occurs much less with low vision.

Besides special treatments for DSL, there is a need for more collaboration between low vision and audiology rehabilitation by, for example, making greater use of referrals [53]. To facilitate this, rehabilitation professionals working in low vision and audiology need interdisciplinary training, to enable them to detect problems associated with DSL and to refer patients as required.

In conclusion, until now, insufficient attention has been paid to the problems of elderly with DSL. However, the development of this DSL protocol represents an important step to improve the health and quality of life of DSL patients.

## Abbreviations

DSL: Dual sensory loss; HA: Hearing aid; OT: Occupational therapist; RCT: Randomized controlled trial.
